## Abstract

**Background:**

While early programs to prevent aggression and violence are widely used, only a few controlled trials of effectiveness of psychoanalytically based prevention programs for preschoolers have been evaluated. This study compares ‘Faustlos’ (a violence prevention program) and ‘Early Steps’ (a psychoanalytically based, whole daycare center intervention to prevent violence) in daycare centers in socioeconomically deprived neighborhoods.

**Methods/Design:**

Preschoolers in 14 daycare centers in Frankfurt, Germany, participate in a cluster randomized controlled trial (CRCT). The daycare centers were randomly chosen from a representative baseline survey of all Frankfurt’s daycare centers carried out in 2003 (*n* = 5,300) with the following stratifying factors: children’s aggressiveness, hyperactivity, anxiety and socioeconomic status. Additionally, the geographic identification of socioeconomically deprived neighborhoods regarding low-income children was taken from the Frankfurt Municipality Statistics. Children’s attachment classification and children’s aggressiveness, hyperactivity, anxiety and social competence are measured as outcome criteria before and after 2 years of intervention. The programs in the study aim to reach a high-risk population. Therefore, the combination of a random sampling of daycare centers out of a representative baseline survey in all daycare centers in Frankfurt and the application of official data on the local distribution of low-income children are unique features offered by the EVA study design. Data on preschooler’s attachment representations are collected in socioeconomically deprived neighborhoods for the first time.

**Trial registration:**

DRKS-ID: DRKS00003500

## Background

Low socioeconomic status (SES) [1-4] and neighborhood deprivation [5,6] have broad effects on children’s mental health and development. Neighborhood deprivation is associated with emotional and behavioral problems even at preschool age [7] and also disrupts children’s ability to develop school readiness [8]. Reviews of early risk factors emphasized interactive effects of aggressive behavior and delinquency as stable patterns over time with onset at early age [9].

At the same time, a growing body of research proposes that the early years of life are a particularly promising time to intervene in the lives of economically disadvantaged children, generating benefits far in excess of program costs [10-15].

In a meta-analysis, 20 early intervention programs targeting at-risk children with low-income or low-SES background have been shown to improve cognitive, emotional and behavioral, development and to reduce levels of delinquency and crime in adulthood [16]. The findings of 34 preschool prevention programs for disadvantaged children indicate positive impacts in the short, medium and long term [17,18].

Previous reviews have suggested that the following characteristics improve program effectiveness: comprehensive, multi-component programs [9,16,19-21], a duration of more than 6 months [22], and early onset in the child’s life [9,20,23,24]. Moreover, minority status (for example, ethnic background) and SES were found to be moderator variables in interventions [16,25].

The early prevention of violence, the enhancement of social learning and the support of the social integration of children were the aims of several prevention studies conducted by the Sigmund Freud Institute in cooperation with the Institute for Analytical Child and Adolescent Psychotherapy and the Municipal Education Authority in previous years, adopting the insights of these mostly US-based prevention studies. A first representative study, the Frankfurt Prevention Study (FPS), was carried out in 14 daycare centers in Frankfurt from 2003 to 2006 with children from low-SES, middle-SES and high-SES backgrounds. It was shown that aggressiveness (*P* = 0.02) and anxiety (*P* = 0.03) in boys and girls, and hyperactivity only in girls (*P* = 0.001) showed a statistically significant reduction in the prevention group in comparison to the control group [26].

The study ‘Evaluation of two prevention programs ‘Early Steps’ and ‘Faustlos’ in daycare centers with children at risk’ (EVA) compares the differential effects of two established prevention programs. Both prevention programs have been rigorously evaluated in the past [26-30]. The EVA study aims at reviewing whether the additional expenses for prevention program 1, Early Steps, is justified in the short and long term in comparison to prevention program 2, Faustlos. Taking into account one of the major findings of the large Head Start program [31], we formulated as one of our main hypotheses that, for children with a high developmental risk (for example, with a disorganized attachment pattern), the standardized, non-individualized Faustlos program will prove not to be sufficient for improving the social integration and the prevention of aggression of these children. We hypothesize that the more complex, individualized and costly Early Steps program will show positive effects on the social behavior of children at risk developmentally. Moreover, we expect the institutional setting/structure of the daycare centers to be a moderator variable. By this, we mean that the institutional setting of the daycare center (management style; participation possibilities for parents; quality of team work among teachers; fluctuation of teachers; frequency of families with multiple problems; open, half-open, or closed groups of children) influences the fit between daycare center and prevention program. For example, a daycare center with the following characteristics: a strict, top down management style, restricted/limited parent participation, high teacher fluctuation, but low frequency of families with multiple problems, might show a better fit to the Faustlos program and, therefore, might show better results in preventing aggression instead of the Early Steps program in a daycare center with the same characteristics.

## Methods

### Participants, inclusion and exclusion criteria

#### Cluster level (daycare center)

The multicenter EVA study is carried out in daycare centers with children of low-SES families who face complex, challenging problems such as unemployment, disadvantaged children, and minority status. Trying to reach children at risk with low SES, while simultaneously ensuring representativeness of the sample, we decided to use a cluster randomized controlled trial (CRCT) design in which clusters (daycare centers) are randomized.

Data from the former Frankfurt Prevention Study allowed us to draw a representative sample of all 3 to 4-year-old children in the public daycare centers of Frankfurt (5,300 children; see Table 1). Relevant stratifying variables were children’s aggressiveness, hyperactivity and anxiety as assessed by their daycare teachers as well as SES, operationalized as families’ dependency on financial support by the Frankfurt Municipality paying the monthly daycare center fee. Additionally, data from the Frankfurt Municipality Statistics on disadvantaged children in Frankfurt’s urban districts operationalized as the children’s dependency on social welfare served as a further approach to identify clusters of children at risk. Thus, we included public daycare centers in the city of Frankfurt characterized by low-SES, high-neighborhood-community risk, and frequented by children with high scores in aggressiveness, hyperactivity or anxiety.

**Table 1 T1:** Daycare centers (DCC) and related clusters

**Factor**	**Low socioeconomic status**	**Middle/high socioeconomic status**	**Total**
Hyperactivity high Aggression high	Cluster 1: 12 DCC (5 with high anxiety scores), 6 of them selected for randomization	Cluster 2: 10 DCC (4 with high anxiety scores)	22
Hyperactivity high Aggression low	Cluster 3: 12 DCC (9 with high anxiety scores)	Cluster 4: 9 DCC (8 with high anxiety scores)	21
Hyperactivity low Aggression high	Cluster 5: 5 DCC (2 with high anxiety scores), 2 of them selected for randomization	Cluster 6: 14 DCC (5 with high anxiety scores), 1 of them selected for randomization	19
Hyperactivity low Aggression low	Cluster 7: 14 DCC (9 with high anxiety scores)	Cluster 8: 10 DCC (2 with high anxiety scores)	24
Not specified*	Cluster 9: 12 DCC, 4 of them selected for randomization	Cluster 10: 16 DCC, 1 of them selected for randomization	28
Sum of DCC	55	59	114

*Missing data: data of the ‘observation questionnaire for preschool children’ including scales of aggression, hyperactivity and anxiety could not be collected.

#### Individual level (children)

In all selected daycare centers, all of the children, male and female, between 3 years 0 months and 4 years 11 months of age at the time of recruitment and their parents were approached to participate in our program. We excluded children beyond the age range. Other exclusion criteria were not applied at the individual level.

### Interventions

The methodological requirement of random assignment gave rise to the ethical question of whether one can leave the control group without treatment and support even though the parents are struggling with serious problems concerning family life, parenting, and child development [32]. An alternative method to avoid this suggests that the control group may serve as an experimental group at a later stage of investigation. This approach was not feasible because the time frame of children staying in the daycare centers (from age 3 to 6) was too narrow. We used a second method, offered by Van IJzendoorn *et al*. [32], suggesting that intervention programs may contain several aspects that can be presented to the experimental subjects as well as to the control group without compromising the experimental design. Therefore, the EVA study compares two intervention programs: the standardized and well validated violence prevention program Faustlos, and Early Steps, a broader, more individual, prevention approach that includes Faustlos as one of its components.

#### The ‘Early Steps’ intervention

The multi-perspective and multi-component prevention program [26] Early Steps is characterized by its approach that starts with a detailed understanding of an individual child and its family. Each child is unique, as is each family. This approach is especially helpful if the specific skills and resources of the individual child are taken as the starting point. Hence, a child’s behavior is not seen primarily as ‘dysfunctional behavior’, but rather as the expression of a hidden (unconscious), reasonable, emotional development. Thus, the specific and perhaps conspicuous behavior of a child needs first to be understood and should not be simply disregarded. The aims of the supportive measures of the study are to allow the child to achieve more positive experiences of itself and its attachment figures and to develop its talents in an optimal way. Early Steps is conducted in close cooperation with the Institute for Analytical Child and Adolescence Psychotherapy. All 13 psychoanalytic therapists and supervisors in the study have at least 15 years of clinical experience in treating children and families and supervising groups (except 1 therapist with 5 years of experience). Early Steps consists of different elements:

•Biweekly case supervision of the daycare center team.

•Weekly proposal of counseling and training for educators and parents in the daycare center by experienced psychoanalytic child and adolescent psychotherapists.

•In individual cases, the proposal of therapy for children and their parents within the facilities.

•Faustlos violence prevention program in the second year of the project at the earliest.

•If required, individual mentoring of children by student teachers in their transition from kindergarten to primary school.

#### The ‘Faustlos’ intervention

This violence prevention program (literally translated: ‘without fists’) [29] is the German version of a US program called ‘Second Step’ that has been developed by the Committee for Children in Seattle and is now widely used in Germany and scientifically well researched [30]. The curriculum consists of 28 lessons and focuses on the promotion of empathy, impulse control and anger management. With the help of pictures of different emotional states, the cognition of gesture and body language of other children, as well as of oneself, is trained. Photographs that are shown to the children portray different conflict situations, which are discussed and re-enacted via roleplay. A certified educator of the Faustlos program trained the EVA daycare teachers. The implementation process of Faustlos is being documented.

### Assessments

Teachers evaluate children’s behavior (aggressiveness, hyperactivity, anxiety and social competence) and well-being using the following questionnaires: before (t0 pre), after 12 months, (t1 12 mo), after intervention (t2 post) as well as 1 year after the end of intervention (t3 follow-up): the Caregiver-Teacher Report Form 1½-5 (C-TRF) [33,34], the Strengths and Difficulties Questionnaire (SDQ) [35,36] and the Positive Development and Resilience in Daycare Center’s Daily Routine (PERIK) [37,38], an observational instrument for teachers. Moreover, the Self-Reflective Functioning Scale [39,40] will be applied for the teachers. Parent’s perspective will be evaluated using the SDQ [35,36]. Children’s assessment is conducted before (t0 pre) and after intervention (t2 post), as well as 1 year after the end of intervention (t3 follow-up). Independent and trained psychologists assess children’s intelligence using the German adaptation of Wechsler Preschool and Primary Scale of Intelligence-III Assessment (HAWIVA) [41] and as well as the children’s attachment representation. The Manchester Child Attachment Story Task (MCAST) [42], a narrative story stem task that involves playing with dolls, is a validated, structured measure that evaluates young children’s attachment representations through the use of play scenarios allowing for differentiation between four overall attachment classifications: secure attachment, insecure-ambivalent attachment, insecure-avoidant attachment and insecure-disorganized attachment representations. Measures and time points of assessment are presented in Table 2.

**Table 2 T2:** Assessments

**Measure point**	**Child**	**Teacher**	**Parents**
t0 (pre-study)	MCAST, HAWIVA	C-TRF, SDQ, PERIK	SDQ
t1 (12 months)		C-TRF, SDQ, PERIK	
t2 (post study, 24 months)	MCAST, HAWIVA	C-TRF, SDQ, PERIK, SRS	SDQ, interview
t3 (follow-up, 36 months)	MCAST, HAWIVA	C-TRF, SDQ, PERIK	SDQ

*C-TRF* Teachers Report Form, *HAWIVA* Wechsler Preschool and Primary Scale of Intelligence-III Assessment, *MCAST* Manchester Child Attachment Story Task, *PERIK* Positive Development and Resilience in Daycare Center’s Daily Routine, *SDQ* Strengths and Difficulties Questionnaire, *SRS* Self-Reflective Functioning Scale.

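### The C-TRF 1½-5 is scheduled at 36 months, when no child is still within its named age range, and at 24 months, when every child recruited at 4 years or older is outside it

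*Protocol article*

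**What the plan says.** All references are to the protocol article.

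- **Individual level (children):** children are eligible "between 3 years 0 months and 4 years 11 months of age at the time of recruitment". Age is the only individual criterion: "We excluded children beyond the age range. Other exclusion criteria were not applied at the individual level".
- **Assessments:** the teacher questionnaires are "the Caregiver-Teacher Report Form 1½-5 (C-TRF", the SDQ and PERIK. They are given before the intervention, at 12 months, after the intervention, "as well as 1 year after the end of intervention (t3 follow-up".
- **Table 2:** the teacher column lists C-TRF, SDQ and PERIK in all four rows, including "t2 (post study, 24 months" and "t3 (follow-up, 36 months". The parent SDQ is listed at t0, t2 and t3.
- **PERIK** is introduced as "Positive Development and Resilience in Daycare Center’s Daily Routine (PERIK) [37,38], an observational instrument for teachers".
- **Interventions:** a delayed-treatment control was rejected because "the time frame of children staying in the daycare centers (from age 3 to 6) was too narrow". The Early Steps description also foresees children moving on to primary school.
- **Outcome:** MCAST is primary. C-TRF, SDQ and PERIK are secondary.
- **Objectives and hypothesis:** the first hypothesis concerns aggressiveness, hyperactivity and anxiety.

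The article names no other form for older children and does not limit the t2 or t3 C-TRF to children still within its range.

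**The concern.** The C-TRF carries its age range in its name, and the eligibility window and visit schedule are both fixed. Together they place some children outside the range at the end of the intervention and all of them outside it a year later. This is a conflict between things the article states, not a detail left to a fuller document.

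An out-of-range score has no established meaning on that form. A rating is also hard to obtain, or comes from a different rater, once a child has left the daycare center. The C-TRF is one of the scales behind the first hypothesis, so its post-intervention and follow-up comparisons would rest partly or wholly on ratings that are out of range or missing in a pattern set by age at entry. PERIK at t3 raises a related problem of setting, because it describes the child in daycare routine.

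**Working it through.** The article gives no figure for age at each assessment, so there is nothing to reproduce first. The check is age arithmetic.

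**Inputs.**
- Entry age 36 to 59 completed months (Individual level).
- Visits at 0, 12, 24 and 36 months (Table 2).
- C-TRF upper limit from its name, read generously as 5y11m, or 71 completed months.
- Daycare stay from age 3 to 6 (Interventions).
- Seven centers per arm with a mean of 17 to 20 children (Power analysis).
- Assumption: t0 is close to recruitment. A later t0 makes the children older and the misfit worse.

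**Step 1. Age at visit = entry age + visit month.**

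| Visit | Youngest | Oldest | Aged 6 or older, even spread |
|---|---|---|---|
| t0 | 3y0m | 4y11m | 0% |
| t1 | 4y0m | 5y11m | 0% |
| t2 | 5y0m | 6y11m | 50% |
| t3 | 6y0m | 7y11m | 100% |

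**Step 2. Range at t3.** The youngest eligible child is 36 + 36 = 72 months, one month above the limit of 71. The 100% therefore holds for any age distribution.

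**Step 3. Range at t2.** A child is out of range when entry age + 24 is at least 72, that is, when entry age is at least 48 months (4y0m). The out-of-range share equals the share recruited at 4y0m or older:
- evenly spread over the 24 monthly ages: 12/24 = 50%;
- weights falling linearly from 24 to 1: (12 + 11 + … + 1)/(24 + 23 + … + 1) = 78/300 = 26%;
- weights rising linearly from 1 to 24: (13 + 14 + … + 24)/300 = 222/300 = 74%.

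**Step 4. Children per arm.** 7 × 17 = 119 and 7 × 20 = 140. With no dropout, the number out of range at t2 per arm is:
- even spread: 0.50 × 119 to 0.50 × 140, about 60 to 70;
- across the two skews: 0.26 × 119 = 31 up to 0.74 × 140 = 104.

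At t3 it is all 119 to 140.

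**Step 5. Daycare stay.** If the stay ends at the sixth birthday, every child is at or past it at t3. If it includes the whole of age 6, every child at t2 (at most 6y11m) could still attend, and only those aged 7 or older at t3 are clearly past it. Those are again the children recruited at 4y0m or older, 50% with even spread. The C-TRF result does not depend on this choice.

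**The case against.** The strongest reply is that the problem is narrower than it looks, and most of that reply stands.

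- **Only one scale is shown to be out of age range.** A reader might infer that all the teacher scales are unsuitable. The article gives no age range for SDQ or PERIK. The PERIK point is about setting only, and rests on its name and the stated daycare stay.
- **The stay is ambiguous.** A reader might infer that no daycare teacher sees any child at t3, that the same is largely true of the older children at t2, or that these children cannot receive a full two-year program. None of this follows if the stay includes age 6. Table 2 says only that a teacher rates, and who rates after the move to school may be settled in the full protocol.
- **The size at t2 is not known.** Half is an assumption about entry ages.
- **The outcomes are secondary.** MCAST is assessed by independent psychologists and is unaffected. The first hypothesis also has the teacher SDQ at all four visits and the parent SDQ at three.
- **Both arms are affected alike.** A reader might infer a biased comparison between programs. The article shows no mechanism that differs by arm. Aging out of the form and changing rater disturb change over time within a child, but do not by themselves favor either program.

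The core is not answered: Table 2 positively assigns the C-TRF 1½-5 to visits at which the article's own ages put children outside it. Similar misfit in both arms does not make an out-of-range score valid. With only 14 centers, the age mix may also differ between arms by chance.

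**Conclusion.** The point holds for the C-TRF. At 36 months all children are outside its named range; this is exact, given t0 close to recruitment and the generous reading of the upper limit. At 24 months every child recruited at 4y0m or older is outside it: 50% under evenly spread entry ages, about 26% to 74% under linear skews.

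For PERIK the point is conditional. At t3 children are at or past the end of the stated stay, or, if the stay includes age 6, only those aged 7 or older are clearly past it.

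The consequence is reduced validity and precision of secondary teacher-rated outcomes in both arms. The article does not support a claim that the primary outcome is compromised, that the first hypothesis is left without usable data, or that the between-arm contrast is biased. The schedule should be amended, which is still feasible because the article reports recruitment as ongoing.

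**What to change.** 1. Remove the C-TRF 1½-5 from t3 in Table 2, and PERIK at t3 for children no longer in daycare.
2. At t2, analyze the C-TRF only in children still within its age range, defined as those recruited before 4y0m. Age at entry is a baseline characteristic that the programs cannot alter.
3. Name the teacher SDQ, already collected at all four visits, as the common behavior scale for the t2 and t3 between-arm comparisons in all children. Since the article gives no age range for the SDQ, confirm that the version used covers ages up to 7y11m.
4. Include age at entry as a baseline covariate.
5. Use rater setting (daycare or school) only in a sensitivity analysis. It arises after randomization, so adjusting for it in the main model could introduce bias.

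Taking t1 as the endpoint for older entrants is not a good alternative. It would mix 12-month and 24-month exposure, and Early Steps brings in its Faustlos component in the second year at the earliest.

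**Cost.** An amendment to Table 2 and its wording, with less data collection at t3. There is no C-TRF follow-up at 36 months, and the C-TRF sample at 24 months is smaller. With even spread, the in-range group is about 8.5 to 10 children per center, or 59.5 to 70 per arm. The article's own formula with CV = 0.467, ICC = 0.0465 and n = 63 (assuming CV and ICC carry over to the subset) gives:
- m = 10: [1 + (1.218 × 10 − 1) × 0.0465] × 63 = 95.8 per arm;
- m = 8.5: [1 + (1.218 × 8.5 − 1) × 0.0465] × 63 = 90.4 per arm.

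The t2 C-TRF comparison would therefore fall short of 80% power for d = 0.5 and should be reported as supportive, with the SDQ carrying the behavior comparison.

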### Objectives and hypothesis

The purpose of the trial is to investigate the differential efficacy of the two intervention programs in a high-risk population. The first hypothesis assumes that the program Early Steps, which individually addresses the child’s particular needs, is more effective than the standardized curriculum Faustlos in preventing aggressiveness, hyperactivity and anxiety. Secondly, we hypothesize that the more restricted approach of Faustlos might better meet the teachers’ demand for structure in some daycare centers depending on the institutional setting. Therefore, we are also interested in investigating the effectiveness of the prevention program in relation to its actual fit to the needs of the institution. Thirdly, we hypothesize that a subgroup of children in the program Early Steps will exhibit a change in their insecure attachment representation towards one that is more structured or secure.

